### Power Calculation to Determine Sample Size

Based on the observational pilot data discussed above, which demonstrated a 50% incidence of day 1 subclinical acute kidney injury in patients receiving <1000 ml of intravenous fluids and a 20% incidence of acute kidney injury (AKI) in patients receiving >2500 ml of intravenous fluids, we anticipate that 39 patients would be required in each arm to detect a similar magnitude of difference with 80% power and a significance level of 0.05. Allowing for 10% attrition, we intend to recruit a total of 86 patients.

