### Randomisation and study groups

A computer-generated 1:1 allocation sequence will be created by an independent operator who is not directly involved with the study. Allocation concealment will be achieved using sequentially numbered sealed opaque envelopes. Allocation to treatment arms will be performed by a member of the research team on the day prior to surgery, after the patient has provided valid written consent.

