### Data Collection

Data will be obtained from the ward observation and fluid charts, anaesthetic record, recovery room observation chart, laboratory and bedside blood test results, intraoperative data collection and clinical review in the post-operative period. To avoid any bias, the outcome assessor will be blinded to the fluid hydration that the patient received. The data that will be collected includes demographic data, patient details, perioperative details and primary and secondary outcome data [Table 1].

**Table 1 Tab1:** Data to be collected

Donor and Recipient Demographic Data	Age Gender Ethnicity Weight Body mass index
Recipient Details	Comorbidities Indication for transplant
Perioperative Details	Volume of donor fluid intake—oral and intravenous Preoperative donor urine output Intraoperative donor urine output Donor fluid boluses and response to fluid challenge. Surgeon performing the operation Duration of surgery Cold and warm ischaemic times
Primary and Secondary Outcome Data	Donor NGAL and BNP (4 measurements): preoperative (day −1), immediately preoperative (day 0), immediately postoperative (day 0), postoperative (day +1) Recipient NGAL (3 measurements): preoperative (baseline), immediately post-operative, postoperative (day +1). Donor eGFR: days 1–4, week 6 and 1 year Recipient eGFR: week 6 and 1 year Recipient delayed graft function (DGF)—defined as use of dialysis in the first week postoperatively 1 year graft and patient survival in recipient Donor intraoperative haemodynamics (including blood pressure, heart rate, stroke volume index, cardiac index and systemic vascular resistance). Biomarkers of AKI, including N-GAL, KIM-1 and leukocyte subsets, in blood obtained from renal vein during retrieval and implantation surgery Donor and recipient perioperative mortality Donor and recipient perioperative complications (including cardiorespiratory complications, time to first bowel motion, infective complications, length of hospital stay, readmission)

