### Statistical Analysis

Descriptive statistics will be used to describe continuous variables. Results for continuous variables will be reported as mean (+/− standard deviation) or median (interquartile range). The primary outcome, proportion of patients in each group with subclinical acute kidney injury, will be compared using a chi-square test and 95% confidence intervals for the difference in proportions.

If the data for continuous variables follow a Normal distribution, the variables will be compared using a Student’s *t*-test. If data are found to not be Normally distributed, a Mann Whitney *U*-test will be used. Analysis will be performed on an intention-to-treat basis.

Study reporting will be in accordance with the CONSORT guidelines.

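### Secondary plasma NGAL outcomes: unadjusted change scores tested behind a normality check are valid but less precise than baseline-adjusted ANCOVA, which costs nothing to adopt

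*Protocol article*

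**What the plan says.** All places are in the protocol article.

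- **Secondary Outcomes** lists the change in donor plasma NGAL to day 1 and the change in recipient plasma NGAL, both from baseline. Donor BNP is also listed as a change. Renal-vein NGAL is listed as a level.
- **Statistical Analysis** gives one rule for continuous variables: Student's t-test if they are Normal, and a Mann-Whitney test "If data are found to not be Normally distributed". No baseline covariate appears. A confidence interval is promised for the primary difference in proportions only.
- **Data Collection, Table 1** gives the four donor NGAL and BNP samples as "preoperative (day −1), immediately preoperative (day 0), immediately postoperative (day 0), postoperative (day +1"). Neither preoperative donor sample is called the baseline. The single preoperative recipient sample is.
- **Study Design** and **Intervention Group** place the 3 L infusion, in one arm only, between midnight and 8 am before morning surgery. **Randomisation and study groups** places allocation on the day before surgery.
- **Primary Outcome** is a day 1 threshold (plasma NGAL above 153 ng/ml), compared by chi-square.

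**The concern.** Three features of the continuous NGAL analysis deserve attention.

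1. A plain change score subtracts the whole baseline value whatever its correlation with the outcome. When that correlation is modest, subtraction adds noise. In a trial of 86 donors with a dichotomised primary outcome, the continuous NGAL comparison is a natural support for the main result, so lost precision matters.
2. Choosing the test from the trial's own data means that the reported effect measure is not known in advance. The Mann-Whitney branch, as stated, yields no baseline-adjusted effect size.
3. Donors have two preoperative samples and neither is named as baseline. The day-0 sample is taken after allocation and after the infusion window. A change computed from it would mix the effect of the infusion on the baseline value with its effect on the day 1 value.

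**Working it through.** **The plan's own figure.** The only sample size stated is for the binary primary outcome: "39 patients would be required in each arm to detect a similar magnitude of difference with 80% power and a significance level of 0.05". With rates of 50% and 20%, pooled variance and a two-sided test:

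n = [1.960·√(2·0.35·0.65) + 0.842·√(0.50·0.50 + 0.20·0.80)]² / 0.30² = 38.5, so 39 per arm.

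Adding 10% to 78 gives 85.8, so the stated 86. The figure reproduces and is not in dispute. No calculation is given for the continuous NGAL outcomes.

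**Precision of the change score.** The document gives neither an SD for NGAL nor a correlation ρ between baseline and day 1, so ρ is an assumption, shown over a range. With equal variances at both times, and relative to comparing day 1 values alone (= 1):

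- change score: 2(1 − ρ)
- ANCOVA: 1 − ρ² (ignoring the one degree of freedom spent on the covariate)
- ratio: 2(1 − ρ)/(1 − ρ²) = 2/(1 + ρ)

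| ρ (assumed) | Change score | ANCOVA | Ratio | Change-score power where ANCOVA has 80% |
|---|---|---|---|---|
| 0.2 | 1.60 | 0.96 | 1.67 | 58% |
| 0.3 | 1.40 | 0.91 | 1.54 | 62% |
| 0.5 | 1.00 | 0.75 | 1.33 | 68% |
| 0.7 | 0.60 | 0.51 | 1.18 | 73% |
| 0.9 | 0.20 | 0.19 | 1.05 | 78% |

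Below ρ = 0.5 the change score is less precise than ignoring baseline altogether, because 2(1 − ρ) exceeds 1. At ρ = 0.5, matching ANCOVA with 39 per arm would take 39 × 1.33 = 52 per arm.

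For an assumed effect of 0.5 SD and 39 per arm, power at ρ = 0.3, 0.5 and 0.7 is 45%, 59% and 80% with the change score, against 63%, 71% and 86% with ANCOVA. Day 1 values alone give 59%.

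**The normality check.** The two-stage rule was simulated with assumed log-normal NGAL (log-SD 0.5, medians 80 and 130 ng/ml), 39 per arm, a Shapiro-Wilk check and 4,000 runs per setting.

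| ρ (assumed) | Type I error, two-stage | Power, two-stage | Power, always t | Power, always Mann-Whitney | Power, ANCOVA on log NGAL |
|---|---|---|---|---|---|
| 0.3 | 0.048 | 0.65 | 0.64 | 0.65 | 0.77 |
| 0.5 | 0.049 | 0.79 | 0.77 | 0.78 | 0.86 |
| 0.7 | 0.054 | 0.93 | 0.92 | 0.93 | 0.95 |

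Power is at an assumed effect of 0.6 log-SD. The simulation error for a 5% rate is √(0.05 × 0.95/4000) = 0.003, so type I error is at its nominal level. The switch costs no power compared with always using either test; the gap to ANCOVA comes from working with unadjusted, untransformed changes. The check was passed in 11% to 25% of runs with no effect and 18% to 32% of runs with an effect. Under these assumptions, which measure is reported is therefore partly a matter of chance.

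**The donor baseline.** If the infusion lowered day-0 NGAL by a fraction f and that sample were the baseline, the apparent rise in the fluid arm would grow by f × baseline. With f assumed at 5% to 20% and baseline at 60 to 100 ng/ml, this is 0.05 × 60 = 3 to 0.20 × 100 = 20 ng/ml, against the fluid arm. With a sample drawn before the infusion, the shift is zero.

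**The case against.** The strongest reply is that nothing here is invalid. Under randomisation, a change from day −1 is an unbiased basis for comparison, and ANCOVA is an improvement in efficiency. These are secondary outcomes. The size of the gain rests on a correlation that the document does not give, and at ρ = 0.9 it is only 5%. All of this stands, and it limits the point to a free improvement.

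A reader might infer more, in three ways that the document does not support:

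- *That the NGAL result will be biased.* No section says that the day-0 sample will be subtracted. Table 1 leans the other way: the plain preoperative label given to the donor day −1 sample is the one attached to the recipient baseline. Which visit is baseline may also be settled in an analysis plan not shown here. The bias is conditional.
- *That the normality check invalidates the test.* The simulation shows no inflation of type I error.
- *That every NGAL outcome is affected, or that recipients are affected most.* Renal-vein NGAL is a level. Recipients have one labelled baseline, and the infusion goes to donors. The efficiency loss depends on ρ, for which there is no recipient figure either.

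It may also be said that a log-scale analysis replaces the listed outcome. On the untransformed scale it does not: regressing the change, or the day 1 value, on arm and baseline gives the same treatment estimate. The log scale does change the measure, to a ratio. That choice is reasonable for a skewed biomarker, but it must be fixed in advance.

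**Conclusion.** The point holds as an improvement to the secondary analyses of donor and recipient plasma NGAL. The planned comparison is valid but has 1.05 to 1.67 times the variance of baseline-adjusted ANCOVA for ρ from 0.9 down to 0.2, assuming equal variances at both times. The normality check leaves the effect measure to the data without harming the error rate. Naming the donor baseline is a safeguard: the 3 to 20 ng/ml shift rests on assumed dilution and baseline values, and arises only if the day-0 sample is used. The primary chi-square comparison, the 39 per arm and the total of 86 are untouched. Confidence is high on what the text fixes and on the direction of the efficiency loss, and low on its exact size.

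**What to change.** In Statistical Analysis, replace the normality-gated choice of test for outcomes that have a baseline value:

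- Analyse log post-operative plasma NGAL (day 1 for donors) by ANCOVA on arm and log baseline NGAL. Report the ratio of geometric means with a 95% confidence interval. If the original scale is preferred, state that in advance and report the adjusted mean difference.
- Apply the same model to recipient plasma NGAL, using its labelled baseline, and to donor BNP.
- Name the day −1 sample as the donor baseline for NGAL and BNP, and state that it is drawn before any infusion starts. Keep the immediately preoperative day-0 value as a post-randomisation measurement, not a baseline.

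The cost is a few sentences of wording. Every value needed is already in Table 1, and no sample, visit or participant is added.

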## Discussion

As there is currently relatively little data about preoperative fluid use in laparoscopic donor nephrectomy, it is hoped that this study will provide important clinical information. Prior to this study, trials looking at preoperative fluids have shown a beneficial effect on intraoperative haemodynamics. In this study, plasma NGAL will be used to determine whether this effect translates to a reduction in subclinical acute kidney injury, which may be of benefit for both the donor and the recipient.

In terms of the volume of intravenous fluid administration, Mertens zur Borg et al. based the volume of fluid administered on ideal body weight [44]. Though this is a useful approach in terms of monitoring the relative effects of fluid on patient physiology, it was decided that in this study a pragmatic approach to this would be the most feasible option. As approximately 3 L of intravenous fluid has been administered preoperatively previously, it was decided that this volume would be used. This is useful both in terms of facilitating adherence to the protocol and in terms of potential future clinical utility, as it would be more easily reproduced in future clinical practice, should any clinical benefit be found.

It is hoped that, whatever the findings of the study, the results will be of real clinical relevance. If preoperative intravenous fluids are found to be of benefit, then this could lead to their widespread use in clinical practice. If, however, no difference is found between the groups, then live donors may not need be admitted to hospital until the morning of the surgery which would mean greater patient convenience and reduced costs.

## Abbreviations

AKI: Acute kidney injury
CI: Cardiac index
CKD: Chronic kidney disease
CRH: Compensatory renal hypertrophy
DGF: Delayed graft function
eGFR: Estimated glomerular filtration rate
ESRD: End stage renal disease
IAH: Intra-abdominal hypertension
NGAL: Neutrophil-gelatinase associated lipocalin
SVI: Stroke volume index
SVRI: Systemic vascular resistance index
